## Abstract

**Background::**

Uterine niche is defined as a triangular anechoic structure at the site of the scar or a gap in the myometrium at the site of a previous caesarean section. The main clinical manifestations are postmenstrual spotting and intrauterine infection, which may seriously affect the daily life of nonpregnant women. Trials have shown an excellent safety and efficacy for the potential of mesenchymal stem cells (MSCs) as a therapeutic option for scar reconstruction. Therefore, this study is designed to investigate the safety and efficacy of using MSCs in the treatment for the uterine niche.

**Methods/design::**

This phase II clinical trial is a single-center, prospective, randomized, double-blind, placebo-controlled with 2 arms. One hundred twenty primiparous participants will be randomly (1:1 ratio) assigned to receive direct intramuscular injection of MSCs (a dose of 1∗10^7^ cells in 1 mL of 0.9% saline) (MSCs group) or an identical-appearing 1 mL of 0.9% saline (placebo-controlled group) near the uterine incision. The primary outcome of this trial is to evaluate the proportion of participants at 6 months who is found uterine niche in the uterus by transvaginal utrasonography. Adverse events will be documented in a case report form. The study will be conducted at the Department of Obstetric of Southern Medical University Affiliated Maternal & Child Health Hospital of Foshan.

**Discussion::**

This trial is the first investigation of the potential for therapeutic use of MSCs for the management of uterine niche after cesarean delivery.

**Conclusion::**

This protocol will help to determine the efficacy and safety of MSCs treatment in uterine niche and bridge the gap with regards to the current preclinical and clinical evidence.

**Trial registration number::**

NCT02968459 (Clinical Trials.gov: http://clinicaltrials.gov/).

## Introduction

1

Approximately 210 million women become pregnant annually, and about 140 million newborn babies are born each year around the world.^[1]^ Of these infants, about one-third are delivered by cesarean section in the United States.^[2,3]^ In China, the overall annual rate of cesarean deliveries increased from 28.8% in 2008 to 34.9% in 2014, a mean increase of 1.0% point per year.^[4]^ Although it allows safe in many situations, the risks of severe maternal complications associated with cesarean delivery are higher than those associated with vaginal delivery.^[5]^ These maternal complications include short-term, such as hemorrhage, anesthetic complications, cardiac arrest, wound hematoma, puerperal infection, venous thromboembolism,^[6]^ long-term, such as chronic pelvic pain, pelvic adhesions, infertility, ectopic pregnancy,^[7]^ the next pregnancy, such as scar pregnancy with life-threatening bleeding, spontaneous abortion, preterm birth, small for gestational age fetus, morbidly adherent placenta, dehiscence or uterine rupture,^[8,9]^ and the nonpregnant state, such as abnormal uterine bleeding, postmenstrual spotting.^[10]^

Uterine niche, also called cesarean scar defect, deficient cesarean scar, pouch, or diverticulum, is defined as a triangular anechoic structure at the site of the scar or a gap in the myometrium at the site of a previous cesarean section.^[11]^ It is one of the most common complications associated with previous cesarean section. The diagnosis of uterine niche can be made by transvaginal ultrasonography,^[12]^ and the best time to perform ultrasonography is in the early proliferative phase.^[13]^ The main clinical manifestations are postmenstrual spotting and intrauterine infection, which may seriously affect the daily life of nonpregnant women.^[14]^ The etiopathogenesis of the uterine niche may be a result of suturing technique during previous cesarean section^[15]^ as well as patient-related factors, such as maternal age, number of previously performed cesarean sections, and flexion of the uterus.^[16]^ The incidence of uterine niche has been reported to be 78% in women with a history of 1 cesarean delivery.^[17]^ The treatment includes medical treatment, such as oral contraceptives,^[18]^ and surgical methods, such as hysteroscopy resectoscopic correction,^[19]^ endometrial ablation,^[20]^ laparoscopic surgery,^[13,21]^ and transvaginal repair surgery.^[22,23]^ Although good outcomes are reported in each study, present treatments could not decrease the incidence among women after undergoing cesarean section.

Smooth muscle cells (SMCs) are found within the walls of blood vessels, and organs such as the uterus and urinary bladder.^[24]^ Mesenchymal stem cells (MSCs) are long-lived cells with the ability of both self-renewal and differentiation into multipotential cells, such as osteoblasts, adipocytes, and SMCs.^[25]^ Human MSCs (hMSCs) can be isolated from somatic tissues, such as bone marrow, adipose or fetal tissue, including amniotic fluid, Wharton jelly, umbilical cord, and umbilical cord blood.^[26]^ Recent preclinical studies have found that MSCs play a major role in regulating SMC expression in animal model^[27,28]^ and exert a specialized function in arterial smooth muscle regeneration and functional recovery.^[29]^ Trials have shown an excellent safety and efficacy for the potential of MSCs as a therapeutic option for myocardial infraction.^[30–32]^

Cesarean uterine scar reconstruction is still a tough task for obstetricians and gynecologists. We postulate that MSCs can promote uterine scar reconstruction and reduce uterine niche incidence during cesarean section. To test the hypothesis, we therefore undertake a Phase II clinical trial of the treatment for uterine niche among primiparous women who undergo cesarean section.

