### Participants

2.1

Primiparous women with a singleton pregnancy between the 37th and 42nd week of gestation will be eligible for inclusion if they are aged 21 to 35 years. Gestational age will be estimated in accordance with the guidelines of the American College of Obstetricians and Gynecologists.^[34]^ Participants will come from our maternity clinic. Obstetricians will answer for the information, details, and requirements of the trial. We will exclude participants who met one of the following criteria: multiple gestation, placenta abruption, placenta previa, fibroids, antepartum hemorrhage, preeclampsia/eclampsia, hepatic or renal dysfunction, any systemic uncontrolled disease or inability to provide consent. After being screened for inclusion and exclusion criteria (Table 1), eligible participants will be introduced in the trial. Each eligible participant must provide their informed consent, and then randomly allocated to MSCs or placebo group according to a randomization numbers. Through the interview, the assistant researchers will be responsible to assess and record the participants’ baseline data.

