### Adverse events

2.5

On the basis of clinical severity, all adverse events, including mild, moderate, and severe, will be obtained and recorded at baseline and throughout the 6-month follow-up. Every time when follow-up, the participants will come to the interviewing room where the case report form (CRF) with adverse events will be filled with their feedback and the specialist checks. We will focus on the wound infection, endometritis, or other infections occurring up to 6 months after delivery in both groups. To evaluate tumor formation as a delayed reaction, we will test the tumor markers (CA12–5, CA15–3, CA19–9, and carcinoembryonic antigen) at baseline and 6 months. The principal investigator (ZL) will be responsible for managing the adverse events clinically. All adverse events will be reported to the Adverse Events Monitoring Committee.

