### Sample size

2.6

The sample size calculation is based on the primary outcome. According to previously published study, the proportion of uterine niche is 78% in women with a history of 1 cesarean delivery.^[17]^ We estimated a power of 90% and a 2-sided 0.05 level of significance, and a drop-out rate of 15% is taken into consideration. Finally, we plan to recruit 120 participants (60 in each group) would detect a 15% relative reduction in the primary outcome.

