### Statistical analysis

2.8

For data analysis, all analyses will be performed according to the intention-to-treat principle. Continuous data will be expressed as mean/standard deviation if it meets normal distribution, otherwise it will be presented by medians/interquartile range; categorical data will be expressed as frequency and percentage. In terms of comparison between the 2 groups, 2-tail Student *t* test for continuous data or the Chi-square test or Fisher exact test for categorical data will be used for outcomes. Relative risks and 95% confidence intervals will be calculated for outcomes. To assess changes of outcome levels over time, an analysis of variance (ANOVA) for repeated measures with post-hoc paired *t* tests or Wilcoxon signed rank test will be used for continuous data. Statistical significance is established at *P* < .05. Statistical analysis will be performed using R 3.0.3.

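### Section 2.8 names only unadjusted between-group tests, although maternal age, a possible factor in niche formation, is known for every woman before treatment; adjusting for it would be a small gain at almost no cost

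*Protocol article*

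**What the plan says.** The Introduction says that niche may result from suturing technique and from "patient-related factors, such as maternal age, number of previously performed cesarean sections, and flexion of the uterus". The wording is tentative, and no direction or size is given for any of these factors.

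The design already holds two of them constant. Section 2.3 prescribes one closure technique for all, and section 2.1 restricts entry to primiparous women. Flexion of the uterus is not stated to be recorded before treatment. Age must be, because women "will be eligible for inclusion if they are aged 21 to 35 years".

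Section 2.2 describes 1:1 allocation from a computer-generated list and states no stratification factor.

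For comparisons between the arms, section 2.8 names a two-tailed Student t test for continuous data, and "the Chi-square test or Fisher exact test for categorical data will be used for outcomes". Relative risks with 95% confidence intervals follow, with no covariate mentioned. A separate sentence gives repeated-measures ANOVA with paired follow-up tests for change over time in continuous outcomes.

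Section 2.5 has four tumour markers measured at two times ("carcinoembryonic antigen) at baseline and 6 months").

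**The concern.** When a pre-treatment variable predicts the outcome, an analysis that uses it estimates the treatment effect with less noise than one that ignores it. Here the plan names one such candidate, must hold it for every participant, and then leaves it out of the stated primary comparison. About 51 women per arm are expected to be evaluable, so even a modest gain in precision is worth having if it needs no new data. Naming the covariate now also prevents an argument later over whether to adjust if the arms happen to differ in age.

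The tumour markers raise the same issue in a lesser way. A baseline value is collected, but the between-group test named for continuous data does not use it.

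**Working it through.** **Inputs from the article (section 2.6)**
- Control proportion: "the proportion of uterine niche is 78% in women with a history of 1 cesarean delivery".
- Effect: the planned sample "would detect a 15% relative reduction in the primary outcome", so the MSC arm is at 0.78 × 0.85 = 66.3%.
- Error rates: "We estimated a power of 90% and a 2-sided 0.05 level of significance".
- Drop-out: "a drop-out rate of 15% is taken into consideration", so 60 × 0.85 = 51 evaluable per arm.

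**Assumptions, not in the article**
- Age is uniform on 21 to 35, so its SD is 14/√12 = 4.04 years.
- Age acts through a logistic model. Its odds ratio is unknown, so a range is shown.

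**Step 1: the plan's own figure.** The pooled two-proportion formula for 78% v 66.3% at 90% power and two-sided 0.05 gives 307 per arm, or 307/0.85 = 362 after drop-out. The stated 60 per arm is not reproduced. Reading 15% as percentage points gives 193 per arm (228 after drop-out). Power for the stated effect is 29.6% with 60 per arm and 25.9% with 51. This is the baseline against which any gain from adjustment has to be judged.

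**Step 2: chance imbalance in age.** The SD of the difference in mean age between arms is 4.04 × √(2/51) = 0.80 years.

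**Step 3: gain from age adjustment.** With marginal rates fixed at 78% and 66.3%, the large-sample variance of the age-standardised risk difference is compared with the unadjusted variance. Effective n is 51 divided by the variance ratio.

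| Assumed OR per 5 years | OR across 21 to 35 (OR^2.8) | Variance ratio | Effective n per arm | Power |
|---|---|---|---|---|
| 1.0 | 1.0 | 1.000 | 51.0 | 25.9% |
| 1.5 | 3.1 | 0.979 | 52.1 | 26.3% |
| 2.0 | 7.0 | 0.943 | 54.1 | 27.2% |
| 3.0 | 21.7 | 0.872 | 58.5 | 29.0% |

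The last row implies odds about 22 times higher at 35 than at 21. It is shown only as an extreme, and the conclusion rests on the first three rows.

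In interval terms, the unadjusted standard error is √[(0.78 × 0.22 + 0.663 × 0.337)/51] = √(0.3950/51) = 0.0880, a 95% half-width of 17.2 points. At an odds ratio of 2.0 per 5 years it is 0.0880 × √0.943 = 0.0855, a half-width of 16.8 points.

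**Step 4: simulation.** With 10,000 trials per setting and 51 per arm, chi-square was compared with an age-adjusted logistic likelihood-ratio test. Here the odds ratio is per SD of age (2.0 per 5 years is about 1.75 per SD).

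| OR per SD | Power, chi-square | Power, adjusted |
|---|---|---|
| 1.0 | 25.7% | 26.1% |
| 1.25 | 26.9% | 27.5% |
| 1.5 | 26.4% | 27.6% |
| 2.0 | 26.8% | 28.9% |

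Under no treatment effect, rejection rates were 4.8 to 5.0% for chi-square and 5.2 to 5.4% for the adjusted test. Part of the apparent gain is therefore that test being slightly liberal.

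**Step 5: tumour markers.** Let ρ be the correlation between baseline and 6 months, with equal variances (both assumed). Relative to a single 6-month value, the variance is 1 for a 6-month-only t test, 2(1 − ρ) for a change score, and 1 − ρ² for ANCOVA.

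| ρ | ANCOVA v 6-month t test, 1 − ρ² | ANCOVA v change score, (1 + ρ)/2 |
|---|---|---|
| 0.3 | 0.91 | 0.65 |
| 0.5 | 0.75 | 0.75 |
| 0.7 | 0.51 | 0.85 |

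**The case against.** The strongest reply is that nothing here is wrong. A chi-square or Fisher test is valid under 1:1 randomisation, the Introduction is background and commits the analysis to nothing, and adjusted or supportive models are often set out in an analysis plan, which is not shown. That stands, and it limits the point to an optional improvement. It does not remove the point, because section 2.8 does state the between-group tests, and they are unadjusted.

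Several stronger readings are tempting, and the article does not support them:

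- *That age is an established cause of niche.* The Introduction says only that it may contribute, and gives no effect size. Restricting entry to ages 21 to 35 limits whatever effect exists. Adjustment does not need causation, only prediction, and costs essentially nothing if age predicts nothing (25.7% v 26.1% power in simulation).
- *That chance age imbalance undermines the primary test.* It does not. The unadjusted test and interval already allow for chance imbalance, and an SD of 0.80 years is small.
- *That every outcome is analysed only by an unadjusted two-group test.* Section 2.8 also gives repeated-measures ANOVA for change over time. If that is applied to the markers, the arm-by-time comparison with two time points is a change-score comparison, which does use baseline. ANCOVA is at least as precise as this (last column of step 5), but the gain over a 6-month-only t test is not the only one that applies.

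It is also fair to say that a logistic odds ratio is not the planned relative risk, that type I error at this sample size depends on the method chosen, and that the markers are safety monitoring. The first two are met by standardising to a relative risk and choosing the variance method with care. The third is why the marker point is secondary.

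**Conclusion.** This is a minor efficiency improvement. The stated primary analysis is valid but leaves unused a pre-treatment variable that the article itself names as possibly prognostic. For assumed odds ratios of 1.0 to 2.0 per 5 years of age, adjustment lowers the variance of the risk difference by about 0 to 6% and adds 0 to 2 points of power. The true gain cannot be fixed from the article and may be zero. The figures rest on uniform age from 21 to 35, a logistic age effect, 51 evaluable women per arm, and rates of 78% and 66.3%.

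A reader might infer that adjustment would rescue the trial's power. It would not. The unadjusted requirement is 307 per arm before drop-out, and at a variance ratio of 0.943 it is still about 307 × 0.943 = 290, against 51 expected.

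**What to change.** In section 2.8, before unblinding:

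- Prespecify the primary analysis as a logistic regression of niche at 6 months on arm and maternal age as a continuous term. Report the standardised (marginal) relative risk and risk difference with 95% confidence intervals from a robust or bootstrap variance. This keeps the planned effect measure.
- Keep the unadjusted chi-square test as a sensitivity analysis.
- Do not add flexion of the uterus unless it is recorded before treatment. The number of previous sections should not vary materially among primiparous women.
- Secondarily, compare each tumour marker at 6 months between arms by ANCOVA with its baseline value as covariate.

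The cost is a sentence or two of analysis wording and a little programming, with no new data. The model spends one extra parameter on about 102 women. Type I error should be described as approximately 5%, given the sample size.

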## Methods

2

This phase II clinical trial is a single-center, prospective, randomized, double-blind, placebo-controlled with 2 arms. The protocol has been developed following the Standard Protocol Items: Recommendations for Interventional Trials (SPIRIT).^[33]^ It will be conducted in accordance with the Declaration of Helsinki and all of the enrolled participants will be provided written informed consent. The protocol and the consent form have been approved by the ethics committee of the Southern Medical University Affiliated Maternal & Child Health Hospital of Foshan. All the randomization, allocation, recruitment, intervention, and analysis, etc., will be conducted in Southern Medical University Affiliated Maternal & Child health Hospital of Foshan. The overall trial profile is shown in Fig. 1. It has been registered with ClinicalTrials.gov, NCT02968459 (http://clinicaltrials.gov/).

**Figure 1 F1:**
[figure not shown]
Chart of trial design.

### Participants

2.1

Primiparous women with a singleton pregnancy between the 37th and 42nd week of gestation will be eligible for inclusion if they are aged 21 to 35 years. Gestational age will be estimated in accordance with the guidelines of the American College of Obstetricians and Gynecologists.^[34]^ Participants will come from our maternity clinic. Obstetricians will answer for the information, details, and requirements of the trial. We will exclude participants who met one of the following criteria: multiple gestation, placenta abruption, placenta previa, fibroids, antepartum hemorrhage, preeclampsia/eclampsia, hepatic or renal dysfunction, any systemic uncontrolled disease or inability to provide consent. After being screened for inclusion and exclusion criteria (Table 1), eligible participants will be introduced in the trial. Each eligible participant must provide their informed consent, and then randomly allocated to MSCs or placebo group according to a randomization numbers. Through the interview, the assistant researchers will be responsible to assess and record the participants’ baseline data.

**Table 1 T1:**
[figure not shown]
Eligibility criteria.

### Randomization and masking

2.2

In total, 120 participants will be randomly assigned to 1 of 2 groups in a 1:1 ratio, the MSCs or placebo-controlled groups. Randomization numbers are completed by using the computer-generated list of random numbers. An independent statistician who is involved in neither the treatment nor data collection will randomize assignments in this study. It will be blinded to random allocation of participants to the 2 groups. The final group assignments will be sealed in opaque envelopes. Other than the investigational pharmacist who prepared the study drug, clinical and research staff members will be blinded in this trial. The assessors and statisticians for the data collection and analysis will be also blinded to the assignments.

### Procedures

2.3

On the basis of previous preclinical safety and bioactivity analyses, participants will be randomly assigned to receive direct intramuscular injection of MSCs (a dose of 1∗10^7^ cells in 1 mL of 0.9% saline) (MSCs group) or an identical-appearing 1 mL of 0.9% saline (placebo-controlled group).

Cesarean procedures and care followed usual practices. All participants will be performed by obstetricians from our department using a unified double-layer uterine closure technique with a continuous absorbable polyglycolic 1–0 suture. After suturing the uterine incision, direct local intramuscular injection will be performed in the uterine incision as soon as possible on the operating table. One milliliter will be injected as 20 aliquots of 0.05 mL into each injection site on the incision using 23-gauge needles. Injection sites will be selected near the incision at evenly 20 different sites (Fig. 2).

**Figure 2 F2:**
[figure not shown]
Direct intramuscular injection sites. (A) Real scene showing injection sites; (B) Schematic drawing showing injection sites. Injection sites will be selected near the incision at evenly 20 different sites.

The MSCs are obtained from the umbilical cord of a healthy donor after delivery. All donors must be provided written informed consent. All procedures for cell processing are carried out according to Good Manufacturing Practice from Health-Biotech Pharmaceutical Company (Guangzhou, China).

MSCs release criteria for clinical use will be as follows: absence of pathogen contamination (bacterial, fungal, viral, or mycoplasma); viability >80% as evaluated by trypan blue staining; immune phenotype, showing the expression of CD73, CD90, and CD105 (Src homology-2) surface molecules (95%); and absence of CD45, CD34, CD11b, CD19, and HLA-DR markers (<2%).

### Outcome

2.4

#### Primary outcome

2.4.1

As a primary outcome of this clinical trial, we will evaluate the proportion of participants at 6 months who is found uterine niche in the uterus by transvaginal utrasonography.

The ultrasound examination will be performed using a 4 to 9 MHz convex transvaginal probe of Voluson E8 (General Electric Medical Systems, Chicago, IL). The niche is defined as a triangular anechoic area at the presumed site of incision.^[35]^ The standardized approach for imaging and measuring niche will be used as described in detail in a previous publication.^[12]^ Meanwhile, the following niche parameters, such as width of the triangular hypoechoic scar niche (W), depth of the triangular hypoechoic scar niche (D), length of the triangular hypoechoic scar niche (L), residual myometrial thickness (RMT), on the transection of the uterus will be also measured (Fig. 3). When the niche is not found, only the RMT value will be measured.

**Figure 3 F3:**
[figure not shown]
Schematic drawing showing niche parameters. (A) Longitudinal section of the uterus; (B) transverse section of the uterus. D = depth of the triangular hypoechoic scar niche; L = length of the triangular hypoechoic scar niche; RMT = residual myometrial thickness; W = width of the triangular hypoechoic scar niche.

